## Abstract

**Background:**

Teens with socially complex needs—those who face multiple and potentially overlapping adversities—are disproportionately affected by several barriers to mental health screening and treatment. Pediatric primary care (PPC) is a typically low-stigmatized setting for teens that is visited at least annually. As such, implementing digital mental health tools (DMH), as low-intensity treatments in PPCs may increase the reach of such tools for teens with socially complex needs.

**Objective:**

This study aimed to evaluate the Teen Assess, Check, and Heal (TeACH) System in comparison to a control condition while integrated into PPCs at 2 Medical Centers serving teen patients in Chicago, Illinois. Through collaboration with key players throughout the design and implementation planning phases, the TeACH System is hypothesized to increase teen patient self-reported engagement with DMH and address specific individual-level barriers to mental health care, compared with a digital psychoeducation control condition.

**Methods:**

Eligible participants will be recruited through PPC clinics housed within the University of Illinois Chicago (UIC) and Rush University Medical Center (RUSH). Recruitment involves invitations from research staff members and primary care clinicians and staff members, as well as posting flyers with QR codes at the specified clinics. All participants complete a brief demographic survey, baseline survey, and Kiddie-Computerized Adaptive Tests Anxiety Module. Participants are randomized to receive either the control condition (digital evidence-based workbook) or the intervention (TeACH System Feedback and Resources). All randomized participants will then be invited to complete an immediate and 1-week follow-up survey. The primary outcomes assess changes in engagement with DMH (ie, likelihood to use DMH for anxiety and actual DMH use) and individual-level barriers to mental health care (ie, symptom understanding and confidence to act). Descriptive analyses will be conducted to characterize the sample and usability ratings of the TeACH System. Linear or generalized linear mixed effects regression models will examine differences in primary outcomes over time.

**Results:**

Recruitment began in July 2024 and data collection is expected to be completed by August 2025. To date, 122 teens have assented to complete study activities, 80 have been randomized (an additional 24 teens have had subthreshold anxiety symptoms and were therefore not randomized), and 42 teens have completed the 1-week follow-up assessment.

**Conclusions:**

This study will provide preliminary feasibility data that may inform how the TeACH System and other DMH low-intensity treatments might better engage and support teens with socially complex needs.

**Trial Registration:**

ClinicalTrials.gov NCT05466929; https://clinicaltrials.gov/study/NCT05466929

**International Registered Report Identifier (IRRID):**

DERR1-10.2196/65245

## Introduction

### Background

Even before the multiple endemics occurring since 2020, pediatric mental health disorders and symptoms were the leading causes of disability and negative sequelae for youth [1]. For some time, mental health disorders have been the most common disease of childhood in the United States, surpassing the *combined* rates of multiple pediatric conditions (eg, cancer and diabetes) [2-4]. Despite the tremendous impact of mental health disorders on teens, millions do not receive mental health care [2]. Anxiety is particularly untreated, as up to 80% of youth with a diagnosable anxiety disorder do not receive mental health care [2,3,5]. Most exposed to this failure of mental health care are teens with socially complex needs, those who face multiple and potentially overlapping adversities, such as (1) enduring adverse childhood experiences, (2) residing in a systemically excluded community that experiences disproportionate disparities in health outcomes and health care access, or (3) being minoritized due to socioeconomic status as well as racial, ethnic, gender, or sexual identity or identities [1,6-8]. Teens with socially complex needs have multiple barriers placed between them and mental health care, which the current system is failing to address [9-15]. As such, traditional methods for reaching such teens are not working, resulting in life-long health disparities and a significant public health impact [2,6,7,16,17].

### Digital Tools Implemented in Primary Care to Extend Care Capacity

Pediatric primary care (PPC) is one setting with strong potential as an environment to engage and screen teens with socially complex needs. Indeed, nearly all youth visit a PPC office annually for well-child visits as well as illnesses or injuries that necessitate care (eg, ear infection) [18]. As such, PPC is a centralized and typically low-stigmatized setting for teens of all backgrounds. Mental health care is increasingly warranted in PPC, with the American Academy of Pediatrics recommending universal anxiety screening for all children and adolescents, aged 8-18 years, during PPC visits [19]. However, PPC providers report variable administration of standardized assessment measures [20] and multiple barriers to mental health screening, broadly [20-22]. Further, when mental health needs, such as anxiety, are screened or arise in PPC, pediatricians report multiple barriers to assessing mental health needs and connecting patients to therapy [23,24], adding to the obstacles to care noted above. Even in the case of using a collaborative care model for depression in primary care [25], a pragmatic approach for anxiety that embraces the logistical realities that providers face in delivering mental health screening and ensuing recommendations is lacking [26,27]. A potential solution to these barriers is to incorporate digital mental health tools (DMH) as a low-intensity treatment (LIT) into PPCs. LITs are patient-facing tools that may provide screening, psychoeducation, resources, or combinations of these items. Given the long-standing efficacy of LITs in digital and other delivery mechanisms for mild to moderate symptom presentations (eg, self-help books) [28], DMH LITs have been proposed as a scalable and strategic first-line model of care in PPC and similar care environments [29].

Integrating DMH LITs into spaces that teens already visit, such as PPC, has the potential to increase mental health care reach. However, uptake and subsequent clinical outcomes will not be impacted if teens do not engage with DMH in their daily lives [30]. One problem is a lack of implementation planning early on in the design processes for DMH [31,32]. Also implicated in poor engagement is a failure to address the range of multilevel implementation barriers, spanning from individual-level barriers (eg, problem recognition, stigma, and confidence to act), intervention barriers (eg, usability and relevance), and systemic barriers (eg, accessibility and cost) [24-27,33]. Interventions such as incorporating motivational interviewing [34] and usage incentivizes [35-37] have improved DMH engagement, but diminish scalability [38]. As such, means to target barriers must be identified and harnessed to address poor engagement, the perennial failure of DMH deployment to date.

### Objectives

In this study, human-centered design methodologies and an implementation science framework [39-41] were used to guide the development and implementation of the Teen Assess, Check, and Heal (TeACH System). Through the use of these methodologies and frameworks, the TeACH System was designed to target individual-level barriers to care (eg, feedback to directly respond to problem recognition, stigma, and confidence to act on symptoms), DMH intervention barriers (eg, human-centered design methodologies to optimize usability and relevance), and systemic barriers to care (eg, increase accessibility by integrating in a space already visited by teens, remove cost barrier by providing a freely accessible service and resources) [24-27,33]. Our primary aim was to increase DMH engagement for teens with socially complex needs through: (1) engaging teens and caregivers from the systemically-excluded and underserved communities of Chicago, Illinois, to refine the TeACH System to be engaging, appropriate, and in line with cultural and user needs; and (2) integrating the TeACH System into PPCs serving teens on the West Side of Chicago. The West Side of Chicago was selected for initial implementation planning and integration evaluations as part of a larger body of research focusing on adapting DMH LITs for and with teens living in communities disproportionately inflicted with health disparities, violence exposure, and higher economic hardship (eg, [42]). Through collaboration with key players throughout the design and implementation planning phases, the TeACH System was hypothesized to increase teen patient self-reported engagement with DMH and address specific individual-level barriers to mental health care, compared with a digital psychoeducation control condition. This hypothesis is being evaluated through a pilot feasibility randomized controlled trial in Chicago PPCs, comparing engagement outcomes for teens with anxiety randomized to use the full TeACH System to those who are provided access to a publicly available, digital evidence-based workbook for teens (psychoeducation control) [43,44].

### Procedures

#### Study Design

The study design is a pilot feasibility randomized controlled trial. The participant focus is teen patients in PPCs with anxiety. While universal anxiety screening is recommended [19], pediatric anxiety has a long-standing history of being underrecognized and often untreated [47-49]. Participants first answer initial screening eligibility questions (ie, age, clinic location, and ability to complete and read surveys in English), followed by completing a digital assent. While a waiver of guardian consent was obtained from the institutional review board, participants are able to “opt in” to have a guardian provide consent in English or Spanish, should they elect to do so. Following assent and optional guardian permission, participants complete a brief demographic survey, indicate their preference for future contact (ie, text message or email), and complete a brief assessment of the primary outcomes (Measures section). All participants then complete the Kiddie-Computerized Adaptive Tests (K-CAT) Anxiety Module [50] to ensure eligibility (ie, a score >29 and indicating mild or greater anxiety symptoms). Participants who do not meet these criteria are excluded and offered access to a publicly available, digital evidence-based workbook for teens [43,44]. Participants who do meet the criteria for mild or greater symptoms of anxiety are randomized into either the control arm (digital evidence-based workbook [43,44]) or the Intervention Arm (TeACH System Feedback and Resources). Randomization is automated through the Research Electronic Data Capture (REDCap, Vanderbilt University) platform, and study staff members are blind to allocation. Following a review of these resources, all participants are invited to complete an immediate follow-up survey. One week following this interaction, participants are invited to complete the same follow-up survey. Figures 1 and 2 display the study design flow.

**Figure 1 figure1:**
[figure not shown]
Participant flow through TeACH system trial in pediatric primary care K-CAT: Kiddie-Computerized Adaptive Tests.

**Figure 2 figure2:**
[figure not shown]
Study flow diagram.

#### Setting and Recruitment

Eligible participants are being recruited through PPC clinics housed within the University of Illinois Chicago (UIC) and Rush University Medical Center (RUSH). Both hospital systems’ primary campuses are situated on the West Side of Chicago and serve diverse patient populations [51,52]. Eligible participants are being recruited in clinics through (1) QR codes on displayed and circulated flyers, including sharing of the flyer by PPC pediatricians, trainees, and staff; and (2) invitation from research staff (ie, offered tablet in the clinic waiting room or while waiting in an exam room) or PPC clinicians and staff members.

#### Inclusion and Exclusion Criteria

For study inclusion, participants must be (1) receiving care at the specified clinics at UIC or RUSH; (2) between 13 and 17 years of age; and (3) able to speak and read in English. These inclusion criteria are determined by teen self-report (ie, answering 3 screening questions based on these criteria). Following assent and completion of a demographics and engagement survey (Measures section), final inclusion criteria are assessed based on responses to the K-CAT Anxiety Module. Namely, to be randomized, participants must also meet criteria for mild or greater symptoms of anxiety (ie, K-CAT Anxiety Module score >29) [50]. There are no assessments for comorbidities, nor any exclusion criteria beyond not meeting the inclusion criteria noted above.

#### TeACH System

The TeACH System is a DMH LIT that includes teen patient-facing brief assessment, feedback, and resources for symptoms of anxiety (sample screenshots displayed in Figure 3. Increasing DMH engagement for teens with socially complex needs is the primary aim of the current iteration of the TeACH System. The mechanism to achieve this outcome includes the use of key player involvement throughout the design and implementation planning processes. Consistent with a broad spectrum of community-engaged research practices [53], involvement of teens and caregivers from the West and South Side Communities of Chicago have ranged from 1-time interviews and focus groups to co-design activities, with plans to form a community advisory board for the broader line of research led by this team [42,54,55]. Most relevant to the design of the current iteration of the TeACH System (eg, direct quotes described below), formative usability testing sessions were completed remotely with 10 teens (mean age 15.9, SD 0.99 years; female: n=8, 80.0%; Hispanic or Latino: n=6, 60.0%; Middle Eastern of North African: n=1, 14.3%; White: n=6, 60.0%) and 7 parents of teens (mean age 41.86, SD 8.7 years; female: n=5, 71.4%; Hispanic or Latiné: n=1, 14.3%; Middle Eastern or North African: n=1, 14.3%; Black or African American: n=4, 57.1%) from the West and South Side Communities of Chicago.

**Figure 3 figure3:**
[figure not shown]
Sample screenshots of the TeACH system.

#### TeACH System Assessment

The TeACH System uses the Kiddie-Computerized Adaptive Tests (K-CAT) Anxiety Module to assess teen patient anxiety symptoms [50]. The K-CAT Anxiety Module (youth report; ages 7 to 17 years) uses an item bank of more than 200 items, typically offering 10 questions to a teen user to predict the likelihood of a diagnosis of generalized anxiety disorder (area under the receiver operating characteristic curve=0.83). However, the module is not limited to generalized anxiety disorder and may also be used for general anxiety screening in youth [50]. Future iterations of the TeACH System may use the full K-CAT (ie, assessing anxiety, depression, substance misuse, oppositional defiant disorder, attention-deficit/hyperactivity disorder, mania, conduct disorder, and suicidality), but the current version of the TeACH System is solely assessing anxiety. This decision was driven by input from PPC clinicians and staff members who expressed concern about follow-up mental health care, safety, and workflow disruptions around more expansive digital mental health assessments [23]. Participants in the current study are eligible for randomization with a score greater than 29 on the K-CAT Anxiety Module, indicating mild, or higher anxiety symptoms [50].

#### TeACH System Feedback

Following the completion of the K-CAT, the TeACH System informs users that they will be provided feedback and specific resources that were informed by feedback from “teens in your community.” The feedback provides an infographic that starts by stating: “Your answer tells us that you’ve been feeling anxiety and worry lately,” followed by the validation that “You’re not alone!” Following this, 4 quotes from Chicago teens describe anxiety as: “feeling worry and uneasiness”; “It’s constant!”; “Just worrying about the future”; and “Constantly worried, stressed, and anxious about every day in life!” before proceeding to viewing resources, users are prompted that “When you are feeling symptoms of anxiety, there are resources you can use to help you feel better.” In sum, the feedback section aims to briefly address multiple individual barriers to care, including problem recognition (ie, “Your answers tell us that you’ve been feeling anxiety and worry lately.”), stigma (ie, “You’re not alone!” and quotes from “Teens from your neighborhoods”), and confidence to act (ie, “When you are feeling symptoms of anxiety, there are resources you can use to help you feel better”) [24-26].

#### TeACH System Resources

Following the feedback, users are asked if they would like to receive DMH resources. The resources are all freely accessible online and are presented to participants through both sample screenshots and links to their direct sources (eg, App Store, YouTube, and TikTok). All resources are grounded in evidence-based skills (eg, progressive muscle relaxation and diaphragmatic breathing) and psychoeducation (including brief videos from teens and young adults with lived experience with anxiety). If participants indicate that they do not wish to receive DMH resources, they are asked to provide a reason as to why. If they would like to receive DMH resources, they are asked what types of resources they would prefer (eg, “Breathing Techniques,” “Apps,” and “Learning More”). This checkbox selection allows teens to view the content they wish, as opposed to getting all options at once, which can be overwhelming. Users may also opt to have the resources sent to them at their preferred method of contact (ie, email or text message).

#### TeACH System Platform

The TeACH System is intended to be adaptable and scalable. As such, using a simple but secure platform that may be easily edited at minimal cost was ideal. UIC’s instance of REDCap was therefore selected as the platform to build and manage the TeACH System [56]. REDCap is housed and managed by the University, as is common across multiple university and health care systems. To enhance the aesthetic appeal and engagement of the TeACH System for teen users, the UIC Innovation Center collaborated on its development within REDCap. An interdisciplinary team of researchers applied human-centered design techniques and analysis frameworks to effectively present the survey and maintain participant interaction throughout. They used user journey maps and extensive user testing to ensure a smooth and intuitive survey flow. The team also crafted a distinct visual language for the TeACH System, incorporating contemporary graphic elements inspired by popular social media platforms, calming color choices, and clear, simple language to appeal to the teen audience and put users at ease.

#### Control Condition

Following screening, assent, demographic characteristic assessment, and completion of the K-CAT Anxiety Module, participants randomized to the control condition receive different feedback and resources than those allocated to interact with the full TeACH System. The control condition includes immediate feedback about anxiety symptoms (ie, “Your answers tell us that you’ve been feeling anxiety and worry lately.”). Following this, participants are queried whether they would like access to a digital resource. If they respond negatively, they are prompted to provide their reasoning. If they respond positively, they are provided with a direct link to a free download of an evidence-based workbook for teens with anxiety [43,44].

### Measures

#### Demographics

Following assent, teens are asked to report the following demographic information: name, age, ethnicity (Hispanic or Latiné and Middle Eastern or North African), race, pronouns, gender, preferred language, the reason for visiting primary care, and preferred method for contact (ie, email or text message).

#### Primary Outcomes

The primary outcomes are administered within REDCap and are assessed at 3 time points for all participants: (1) baseline: following assent and before administration of the K-CAT; (2) post interaction: immediately after receiving the allocated feedback and resources; and (3) maintenance: 1 week following the interaction. The primary outcomes are discrete variables focusing on individual-level barriers to mental health care (ie, symptom understanding, confidence to act [24-26]) and engagement with DMH (ie, likelihood to use DMH for anxiety, actual DMH use). Namely, through a questionnaire created for this study, participants rate on a Likert scale (1=not at all to 5=completely): (1) anxiety *understanding* (ie, “I understand what anxiety is.”); (2) *confidence to act* (ie, “I feel confident I can do something if I feel anxiety.”); and (3) *likelihood* to use digital tools for anxiety (ie, “If I feel anxiety, I would use a digital tool to help (app, website, and reel or video).”). Following this, participants indicate whether they have used a digital tool for their anxiety before (ie, yes, no, and unsure).

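### The actual-use primary outcome asks whether a teen has used a digital tool before, so as described it captures only first-time uptake, not renewed or continued use after the intervention

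*Protocol article*

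**What the plan says.** The Abstract (Methods) frames the outcome as one of change: "The primary outcomes assess changes in engagement with DMH (ie, likelihood to use DMH for anxiety and actual DMH use"). Under Measures, Primary Outcomes, the engagement domain is "engagement with DMH (ie, likelihood to use DMH for anxiety, actual DMH use"), and the primary outcomes "are assessed at 3 time points for all participants". The second time point is "post interaction: immediately after receiving the allocated feedback and resources"; the third is "maintenance: 1 week following the interaction".

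The same section describes one measure of actual use: "participants indicate whether they have used a digital tool for their anxiety before (ie, yes, no, and unsure"). It gives no reference period for either follow-up. Procedures, Study Design, adds that at 1 week "participants are invited to complete the same follow-up survey". The article describes no link log, download count, frequency item or follow-up-specific question on use.

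Data Analyses, Overview, models the responses to all three questionnaires in mixed models. It also names existing use of digital tools, and its interaction with time, as covariates. The only described source for that covariate is this same item at baseline.

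**The concern.** The construct is use following the intervention; the item as described asks about any use up to now. An answer to such a question can, if truthful, move only from no or unsure to yes. A teen who had already used a tool at baseline answers yes at 1 week whether or not the offered resource was ever opened. That teen therefore says nothing about use after the interaction.

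The immediate time point has a separate difficulty. Minutes after allocation, hardly anything can have been used except the study content on the screen, so a new yes may record exposure to that content.

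This is the only behavioural measure among the four primary outcomes, in a trial whose stated aim is to raise engagement with digital tools. Information that was not asked for at 1 week cannot be recovered in the analysis.

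**Working it through.** The article states no figure for this outcome, so there is nothing to reproduce. The first part follows from the text; the second is an illustration.

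**What each answer pattern can mean, baseline to 1 week**

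| Baseline | 1 week | What it shows |
|---|---|---|
| No | Yes | First use since baseline |
| No | No | No use since baseline |
| Unsure | Yes | First use, or earlier use now recalled |
| Yes | Yes | Nothing about use since the interaction |

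The information lies in teens who answer no or unsure at baseline.

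**Inputs for the illustration**
- From Sample Size and Power: 300 participants and 15% attrition at 1 week. 300 × 0.85 = 255.
- Assumed: all 300 are randomized, 1:1, giving 255 / 2 = 127.5 per arm; two-sided alpha 0.05.
- Assumed: true use in the week after the interaction is 20% (control) and 35% (TeACH), independent of earlier use.
- Assumed: the share *b* already answering yes at baseline is 30%, 50% or 60%. The article does not give it.

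**Formulas**
- Effect size h = |2·arcsin√p1 − 2·arcsin√p2|. Power ≈ Φ(h·√(n/2) − 1.96), with n per arm.
- Share answering yes at 1 week on the item as described: b + (1 − b)·p. The between-arm difference is therefore (1 − b) times the true difference.
- If the analysis uses baseline status, the informative teens are the baseline non-users, n = 127.5·(1 − b) per arm, compared at 20% versus 35%. This approximates the planned mixed model.

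**Item about use since the interaction:** h = 0.339, n = 127.5, h·√(n/2) = 2.71, power 77%.

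**Item as described**

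| b | Yes at 1 week, control vs TeACH | Difference (points) | Power, raw 1-week proportions | Non-users per arm | Power, using baseline status |
|---|---|---|---|---|---|
| 30% | 44.0% vs 54.5% | 10.5 | 39% | 89.25 | 62% |
| 50% | 60.0% vs 67.5% | 7.5 | 24% | 63.75 | 48% |
| 60% | 68.0% vs 74.0% | 6.0 | 18% | 51 | 40% |

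The raw comparison suffers twice: prior users shrink the difference, and they add noise. Using baseline status removes the second problem but not the loss of informative teens.

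**The case against.** - **The item is not uninformative.** A reader might infer that it cannot show any use after the intervention. The documents do not support that: a change from no to yes at 1 week indicates first uptake. This stands, and it confines the point to renewed or continued use and to the lost information.
- **The lowest power figures do not reflect the plan.** Data Analyses, Overview, models the baseline responses and examines existing use as a covariate, so the raw 1-week comparison is not what is planned. This stands; 62%, 48% and 40% are the fairer figures, and they still fall well short of 77%.
- **The wording is a paraphrase.** The three Likert items are printed verbatim; this one is not, and the sameness of the follow-up survey links the two follow-ups to each other, not to baseline. The fielded follow-up wording could therefore differ. This stands as a caveat, but nothing in the article says that it does differ.
- **A spurious effect at the immediate time point is only possible.** Both arms are offered a digital resource on screen, and it is unknown whether teens would count viewing it as use, or do so differently by arm. A reader might infer a demonstrated bias toward TeACH; the article does not support that. The lack of opportunity for use at that point remains.
- **This is a pilot feasibility trial with three other primary outcomes.** Understanding, confidence and likelihood of use are untouched. This stands and lowers the severity.

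**Conclusion.** The point holds in limited form. As described, the actual-use outcome measures first-time uptake among teens answering no or unsure at baseline. It misses renewed or continued use by prior users, and at the immediate time point it has almost nothing to measure. That much follows from the item and the schedule and needs no assumed rates.

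The size does depend on assumptions: weekly use of 20% versus 35%, 1:1 allocation, 127.5 per arm, independence of past and new use, and baseline use between 30% and 60%. Under these, power falls from about 77% to between 62% and 40% when baseline status is used.

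It would go too far to conclude that the trial cannot address engagement at all: likelihood of use is a second engagement outcome and is unaffected. This should be fixed, because the repair is cheap and the missing information cannot be recovered afterwards. It does not invalidate the trial.

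**What to change.** 1. Add one REDCap question at 1 week: whether the teen has used any digital tool for anxiety since the study interaction, including the resources or workbook offered.
2. Define the between-arm actual-use outcome at 1 week as yes versus no or unsure on that question, with the baseline item on earlier use as covariate.
3. Do not treat actual use as an outcome at the immediate time point.
4. Keep the existing item as a secondary measure of first uptake among baseline non-users, including for teens already followed up.

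If the fielded follow-up item already asks about use since the interaction, state that wording instead; then only steps 2 and 3 need confirming.

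The cost is one survey question and a short amendment. The real downside is that one of four primary outcomes changes mid-trial, and everyone followed up before the amendment lacks the new item. That was 42 teens when the article was written, or 42 / 255 = 16% of the number expected at 1 week, and it will be more by the time an amendment takes effect. The change and its date should be reported.

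### As described, the primary outcome of actual digital tool use cannot separate exposure to the study session from use of a tool afterwards

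*Protocol article*

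**What the plan says.** Under Primary Outcomes, the article lists "engagement with DMH (ie, likelihood to use DMH for anxiety, actual DMH use" among the primary outcomes. Three of the four are Likert items with their wording given. The fourth, actual use, is described as follows: "participants indicate whether they have used a digital tool for their anxiety before (ie, yes, no, and unsure".

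All four are asked three times. The second occasion is "post interaction: immediately after receiving the allocated feedback and resources". For the third, Study Design says that 1 week later "participants are invited to complete the same follow-up survey".

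The TeACH System section places the intervention in the class of tools that the outcome counts: "The TeACH System is a DMH LIT that includes teen patient-facing brief assessment, feedback, and resources for symptoms of anxiety". Its resources are "presented to participants through both sample screenshots and links to their direct sources", with app stores and video platforms as examples. The likelihood item, which comes just before the use item, tells teens what a digital tool is: "I would use a digital tool to help (app, website, and reel or video".

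The control arm is digital too. After the same computerized anxiety test (K-CAT), control teens receive one feedback sentence, and if they want a resource, "they are provided with a direct link to a free download of an evidence-based workbook".

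Sample Size and Power plans a pre-post comparison through the main effect of time and a between-arm comparison through treatment by time. The Data Analyses overview puts all three time points into the mixed models.

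**The concern.** The introduction says that digital tools fail when teens do not use them in daily life, so a use outcome should capture uptake outside the session. As described, the item asks about any previous use. Between its first and second administration, every randomized teen goes through digital anxiety material supplied by the study. A teen who answered no at baseline can then truthfully answer yes without having opened any tool elsewhere.

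Both planned comparisons are exposed. The time effect can rise because the study material was delivered. The treatment-by-time effect can differ from zero if teens in one arm more readily regard what they were shown as a digital tool. The analysis cannot undo this later, because one yes/no/unsure answer does not say which tool the teen had in mind.

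**Working it through.** The plan gives no figure for this outcome, so there is none to reproduce. The check has two parts.

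**What each answer can mean**

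- *Baseline:* asked before the K-CAT and before any study material. A yes is prior use.
- *Directly after the session:* almost no time has passed for use elsewhere. A change from no to yes reflects the session or a changed reading of the question.
- *1 week:* a yes can be prior use, the session, or real use during the week. The answer does not distinguish them.
- Truthful answers to an ever-use question can move only from no to yes, so the contamination pushes the time effect upwards.

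**How large the effect could be**

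Inputs from Sample Size and Power: 300 planned and 15% attrition, so 300 × 0.85 = 255, taking the 300 as randomized. Assumed, because the article does not state them: 1:1 allocation (n = 127.5 per arm), two-sided 0.05, and prior use b. Also assumed: no true effect on outside use, and a share q of prior non-users who count the study material.

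- Reported use in an arm: p = b + (1 − b)q
- Spurious rise from baseline: (1 − b)q
- Spurious difference between arms: Δ = (1 − b)(q_T − q_C)
- Rejection: Φ[(Δ − 1.96·SE0)/SE1] + Φ[(−Δ − 1.96·SE0)/SE1], with SE0 = √[2p̄(1 − p̄)/n] and SE1 = √{[p_T(1 − p_T) + p_C(1 − p_C)]/n}

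Example with b = 50%, q_T = 20%, q_C = 0: p_T = 0.60, p_C = 0.50, Δ = 0.10, SE0 = 0.0623, SE1 = 0.0620. Then (0.10 − 0.1221)/0.0620 = −0.36, and the rejection rate is 36%.

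Between arms, b = 50%:

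| q_T vs q_C | Reported use | Difference (points) | Rejection |
|---|---|---|---|
| 30% vs 30% | 65% vs 65% | 0 | 5% |
| 5% vs 0% | 52.5% vs 50% | 2.5 | 7% |
| 30% vs 20% | 65% vs 60% | 5 | 13% |
| 20% vs 0% | 60% vs 50% | 10 | 36% |
| 50% vs 30% | 75% vs 65% | 10 | 41% |
| 10% vs 20% | 55% vs 60% | −5 | 13% |

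With 20% vs 0% and lower prior use, the difference is 14 points (64% rejection) at b = 30% and 16 points (81%) at b = 20%.

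Pre-post: if 30% of prior non-users count the material, the spurious rise is 0.8 × 30 = 24 points at b = 20%, 0.7 × 30 = 21 at b = 30%, and 0.5 × 30 = 15 at b = 50%. This holds even when the arms count alike.

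These rates come from a two-proportion test at one time point. The planned mixed model would give somewhat different values, but the mechanism is the same.

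**The case against.** Several objections have force.

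- *The item is paraphrased.* The three Likert items are quoted and this one is not. The form may carry an instruction that the article omits, or teens may read the question as meaning before today. This stands as a limit: one can say only that the article shows no exclusion. Checking the form settles it.
- *The control arm has digital exposure too.* Both arms take the K-CAT, both receive feedback on their symptoms, and control teens are offered a digital workbook. This stands. It weakens the between-arm concern but not the pre-post one.
- *The direction is not shown.* A teen may not regard a clinic survey with an infographic and links as a digital tool, and teens who decline resources see only the feedback. This stands. TeACH's apps and videos do match the examples in the preceding item, which makes a bias towards TeACH plausible, but the documents do not establish it.
- *The sizes are assumed.* They are. At a 5-point gap the distortion is slight.
- *This is a pilot, and one outcome of four.* True, but the article claims adequate power for both comparisons, and this is its only measure of reported use.

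Wording and timing cannot be left to an analysis plan, because they are fixed when the data are collected.

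**Conclusion.** The point holds in a limited form. As the article describes it, the use item can count delivery of study material as uptake. The immediate answer carries almost no information on outside use, and the 1-week answer is a mixture. The pre-post comparison is inflated wherever teens count the session. The between-arm contrast is biased only as far as the arms differ in doing so: about 5%, 7% or 36% rejection for gaps of 0, 5 or 20 points, under 50% prior use, no true effect, 1:1 allocation and two-sided 0.05.

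A reader might infer that the outcome is true by allocation in the TeACH arm, or that the error must favour TeACH. The documents do not support either: control teens can also truthfully answer yes, and with equal counting the between-arm rejection rate stays at 5%. Nor do they support a high false-positive rate as an expected result. A 30-point gap at 30% prior use would give 21 points and 93%, but nothing in the article points to a gap of that size.

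**What to change.** First check the REDCap follow-up forms for an instruction that the article does not report. If there is none:

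1. Take the immediate post-interaction time point out of the analysis of actual use. It can stay for the three Likert outcomes.
2. At 1 week, ask about use since the study session of any app, website or video for anxiety. Tell teens not to count the study survey and feedback pages, but to count later use of resources that the study linked to. A blanket instruction to ignore everything shown in the study would be a mistake, because it could exclude the linked apps and videos whose use the trial wants to raise.
3. Record use of the allocated resources as a separate item.
4. Analyse responses under the old wording with wording version as a factor, or report them descriptively.

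The cost is a minor amendment, two wording versions for one of four primary outcomes, and fewer responses in the comparative analysis of use. When the article was written, 80 teens had been randomized and 42 had completed the 1-week survey, so most of the planned 300 could still answer the new item. A since-session question has no baseline counterpart, so use would be compared between arms at 1 week. Prior use would enter as a covariate, as the article already plans, and the pre-post comparison would be dropped for this outcome.
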